### Proposed care models (mechanisms of action)

Figure 3 shows a standard suicide prevention care model (usual care) and the proposed enhanced care suicide risk model (intervention). A typical workflow that involves suicide risk identification, when a patient presents for a behavioral health visit, may begin with suicide risk screening (typically the PHQ9 [42] in the participating sites). If the PHQ9 is missed, refused, or if item 9 (“Over the last two weeks, how often have you been bothered by thoughts that you would be better off dead or of hurting yourself in some way?”) is denied, the workflow may terminate, however a clinician could also proceed if clinically indicated. Potentially terminal processes are indicated by a dark background in Fig. 3, text boxes with white backgrounds indicate continuation of the workflow. The expectation is that when patients respond positively to item 9 (i.e., respond with a score of 2 “more than half the days” or 3 “nearly every day”), a comprehensive suicide risk assessment is conducted (typically the Columbia Suicide Severity Rating Scale [C-SSRS] [43] in the participating sites). Again, if the risk assessment is missed, refused, or if risk is denied the workflow may terminate. The expectation is that when risk is confirmed, depending on acuity, a referral is made to outpatient supportive services or to the emergency department or inpatient setting.

The enhanced care suicide risk model (intervention) demonstrates the proposed changes in workflow with the risk model implementation. In this model, the suicide risk model flags the clinician in the EHR to conduct additional suicide risk screening. The expectation is that if the PHQ9 were missed, refused, or if item 9 was denied in the presence of a model-generated risk flag indicating elevated estimated risk, then the clinician would proceed to the C-SSRS as if the screening were positive.

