Generalized Linear Mixed Models (GLMMs) with logit link function will be used to assess categorical outcomes (identification and recognition, separately, defined as yes/no) to study the effect of the intervention on identification and recognition. The results will be presented as odds ratios (OR) with 95% CIs. We will analyze the frequency of events identified through PHQ-9 (identification), recognized through the C-SSRS (recognition), or both combined. Additionally, GLMMs with a log link function will be used to separately assess the effects on identification and recognition by modeling the count of identified or recognized patients. The model will include the intervention (yes/no) as an independent variable to assess its effect while accounting for clustering and potential confounders. Among visits where individuals are identified or recognized as being at risk, we will further investigate factors influencing these outcomes, including patient demographics and clinical characteristics. The results will be presented as relative risk (RR) with 95% CIs. In these analyses, clusters will be analyzed according to their randomized crossover time. Models will include a random effect for cluster and a fixed effect for each phase, and will adjust for age, sex, race/ethnicity and cluster/clinic terms (i.e., secular trend). These models are optimal and commonly used for studies implementing stepped wedge cluster randomized trial designs [31, 32, 50]. All analyses will also adjust for time, given that the ratio of exposed clinics increases over time, and calendar month to account for seasonality of suicide attempts. Given that patients may be screened or identified as at-risk multiple times, the frequency of visits during the follow-up period will be adjusted in the model as well. In additional analyses, the model will account for cluster effects by clinic and correlation between repeated measurements for the same patient over time.

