These models will also be used to test mediators/mechanisms, given that we hypothesize that identification alone will not reduce suicide outcomes but rather increase the number of people receiving suicide intervention, which could lead to improvement (i.e., decrease) in suicide outcomes. Mechanisms include interaction with the alert and initiation of assessment, which starts the outpatient care pathway. We will also stratify analyses by health system site, and test for mental health diagnoses and prior suicide attempts as moderators. Importantly, we will exclude ‘training’ months for each phase of clinic implementation from the main analyses, since clinicians and patients may be partially exposed as the models are implemented and clinicians trained. In a secondary set of analyses, we will explore potential heterogeneity in treatment effects between clinics. Here we will conduct additional analyses to test within cluster comparisons of exposed and unexposed periods.

To examine the effectiveness of a suicide risk model on health service engagement and suicide attempt outcomes, we will start with similar descriptive and GLMMs analyses proposed previously for identification and recognition. The analyses here will focus on each unique health service engagement (supportive and crisis encounters separately) and suicide attempt outcomes, stratified by exposed (intervention) versus unexposed (control) groups. Suicide attempts will be captured by health system records using ICD-10 diagnosis codes occurring within the same 90-day and 180-day time periods. We will also use a Kaplan-Meier method and Cox-proportional hazards models to examine time-to-event for health service engagement and suicide attempts, with statistical adjustment for clinical and demographic factors. Individuals will be censored at the time of death or at 180 days past the index visit. We will again add terms for calendar month as well as site to account for variation by season and health system.

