Finally, we will separately examine the impact of health care engagement and exposure to ZS evidence-based interventions as mediators of suicide attempt and use of crisis services. We will estimate direct and indirect effects in our longitudinal settings using our previously proposed GLMMs [51]. Specifically, we will test the effect of the intervention (risk model study group, yes/no) on behavioral health service engagement (yes/no within 7 and 14 days via path ‘*a’*) and the effect of behavioral health service engagement on suicide attempt outcome (yes/no within 90 and 180 days via path ‘*b*’). The residual effect of the intervention unaccounted for by behavioral health service engagement will be tested via path ‘*c*’. We will also test a separate path model of exposure to documented suicide prevention interventions and their impact on suicide attempt outcomes using the same modeling approach. These models will include both individual documented supportive outpatient interventions for suicide and multiple interventions bundled together; we will also repeat these analyses for crisis services outcomes.

We will address missing data using multiple imputation or inverse probability weighting, depending on the nature and extent of missingness. Additionally, if the proportion of missing data is substantial, we will conduct sensitivity analyses to assess its potential impact on our findings.

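### Path b of the mediation analysis compares non-randomized care groups with no named baseline risk covariate, so it is open to confounding by severity in either direction

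*Protocol article*

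**What the plan says.** All references are to the protocol article.

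- **Mediation model** (Analysis plan for effectiveness outcomes): "We will estimate direct and indirect effects in our longitudinal settings using our previously proposed GLMMs". Path a runs from the intervention to engagement within 7 and 14 days. Path b is "the effect of behavioral health service engagement on suicide attempt outcome" within 90 and 180 days. Path c is the remaining effect of the intervention. The same approach is used for documented suicide prevention interventions and is repeated for crisis services.
- **Covariates of the reused models** (same section): a random effect for cluster and a fixed effect for phase; they "will adjust for age, sex, race/ethnicity and cluster/clinic terms (i.e., secular trend". In addition, "All analyses will also adjust for time" and calendar month, and "the frequency of visits during the follow-up period will be adjusted in the model as well".
- **Clinical history** (same section): past-year attempt and current diagnoses are described by exposure group, and diagnoses and prior attempts are tested as moderators. Neither is listed as an adjustment in the mediation models.
- **How care is allocated** (Proposed care models): "when risk is confirmed, depending on acuity, a referral is made to outpatient supportive services or to the emergency department or inpatient setting". The same section says that care after the assessment depends on its result and on clinical judgement.

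**The concern.** The covariate list was written for the effect of the intervention. Clinic crossover order is randomized, so that effect and path a do not need a rich set of patient risk factors. Path b is a different contrast: engaged against non-engaged patients, at the same intervention status. Assessed risk influences who is engaged, and it strongly predicts attempts. Unless risk is in the model, path b mixes any effect of care with the reason the care was given. Placing the contact strictly before the attempt does not remove this.

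The error spreads. The indirect effect is built from paths a and b, and path c conditions on the same confounded mediator. The analysis tests the article's stated mechanism, that the risk model works by bringing more people into care. A distorted path b could wrongly discredit outreach, safety planning, means counseling or caring contacts, or wrongly credit them.

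**Working it through.** **Inputs from the article.** N = 395,000 patients, 0.6% with an attempt within 90 days, and 4–5% at high risk (4.5% used), from Sample size and power analysis; C-statistics of 0.83 to 0.86, from Background.

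**Assumed, because the article does not give them.** Contact rates: 30% in other patients and 20% to 70% in high-risk patients.

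**1. The article's own figure.** 0.006 × 395,000 = 2,370 attempts, as stated. No figure is given for the mediation analysis.

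**2. Attempt risk by stratum.** Take a binormal score with C-statistic 0.85, so the separation is √2 × Φ⁻¹(0.85) = 1.466. The top 4.5% then captures 40.0% of attempts.
- High risk: 0.045 × 395,000 = 17,775 patients, 0.400 × 2,370 ≈ 949 attempts, risk 5.34%.
- Others: 377,225 patients, 1,421 attempts, risk 0.377%.
- Risk ratio: 5.34 / 0.377 ≈ 14.

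**3. Crude path b when contact has no effect.** For contact of 50% against 30%:
- contacted: 0.5 × 17,775 + 0.3 × 377,225 = 122,055 patients; 0.5 × 948.6 + 0.3 × 1,421.4 = 900.7 attempts
- not contacted: 272,945 patients; 1,469.3 attempts
- odds ratio = (900.7 / 121,154.3) / (1,469.3 / 271,475.7) = 1.37

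| Contact, high-risk vs other | Odds ratio (C = 0.85) | Range for C = 0.83 to 0.86 | Two-sided 5% test rejects |
|---|---|---|---|
| 40% vs 30% | 1.18 | 1.16–1.19 | 96% |
| 50% vs 30% | 1.37 | 1.32–1.40 | 100% |
| 70% vs 30% | 1.83 | 1.71–1.91 | 100% |
| 20% vs 30% | 0.84 | 0.86–0.83 | 97% |

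The rejection column is for C = 0.85. In every row the true odds ratio is 1.

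**4. Crude path b when contact helps.** The same two-stratum table, with assumed attempt risk ratios (high-risk to other) of 5, 10 and 20:

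| True odds ratio | 40% vs 30% | 50% vs 30% | 70% vs 30% |
|---|---|---|---|
| 0.8 | 0.86, 0.91, 0.99 | 0.92, 1.03, 1.19 | 1.04, 1.29, 1.70 |
| 0.6 | 0.64, 0.69, 0.74 | 0.69, 0.77, 0.90 | 0.78, 0.97, 1.29 |

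The benefit is diluted in every cell. It changes sign only where the confounding is strong enough to outweigh it.

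**5. Does follow-up visit frequency repair it?** One simulated data set per setting (400,000 patients, about 2,400 events), with a continuous baseline risk (log odds ratio 1.0 per SD for attempt) and visits that rise with risk and with engagement. All coefficients are assumed, and clinic effects are omitted.

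| Engagement log odds ratio per SD of risk | True odds ratio | Demographic covariate | + visit frequency | Demographic + baseline risk |
|---|---|---|---|---|
| 0.4 | 1.0 | 1.47 | 1.27 | 1.00 |
| 0.4 | 0.8 | 1.19 | 1.02 | 0.82 |
| 0.2 | 1.0 | 1.21 | 1.08 | 0.99 |
| 0 | 1.0 | 1.04 | 0.94 | 1.04 |
| −0.2 | 1.0 | 0.75 | 0.70 | 0.91 |

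Visit frequency lowers the estimate in every row. With positive confounding that happens to move it toward the truth, but not all the way. With no confounding (fourth row) it still shifts the estimate, from 1.04 to 0.94, because it is counted after the index visit and depends on engagement. With reversed confounding it moves the estimate further from the truth. Each row is a single run, so departures such as 1.04 or 0.91 in the last column include simulation error (a standard error of about 0.04 to 0.05 on the log scale in tables of this size).

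**The case against.** **This belongs in an analysis plan.** A condensed article need not list mediator–outcome confounders, and it cites a mediation method that is not shown. That would hold if the article were silent. Instead it names a covariate set and carries it to a contrast that the set was not built for. Two phrases might seem to fill the gap. The phrase "while accounting for clustering and potential confounders" is unspecified and stands in the text on the intervention's effect on identification and recognition. The phrase "with statistical adjustment for clinical and demographic factors" is attached to the Cox models, not to the mediation models.

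**The plan does not adjust for demographics alone.** This stands. A reader might infer so, but clinic, phase, time, calendar month and visit frequency are also in the model. What can be said is that demographics are the only baseline patient characteristics named.

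**The direction is not known.** This stands too. The workflow sends confirmed risk either to outpatient services or to emergency or inpatient care, and the article expects some at-risk patients to miss or refuse screening. If the most acute patients have less outpatient contact, the bias runs toward benefit.

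**The size is crude.** Also fair. The odds ratios near 1.2 to 1.8 come from a two-by-two table over all patients, with no covariates, and are not the bias of the planned model. Contact is timed from an index visit that the article also calls the risk identification encounter. If mediation is run only among flagged patients, N is about 17,775 and the two-stratum contrast gives 1.00 by construction. Confounding by acuity could remain within that group, but it is not quantified here. The primary outcome's denominator is all visits, so the text leaves the mediation population open.

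**Conclusion.** The point holds in a limited form. As written, path b is a non-randomized comparison in a setting where care follows assessed risk, and no baseline measure of that risk is named in the model. Path b, the indirect effect and path c are open to confounding by severity, as are the parallel models for documented interventions and crisis use.

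Under no true effect, the illustrative crude odds ratio is about 1.2 to 1.8 if high-risk patients are contacted more (40% to 70% against 30%) and about 0.84 if they are contacted less (20% against 30%). These figures rest on assumed contact rates, a 4.5% high-risk share and a C-statistic of 0.85.

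Two stronger readings are not supported. One is that engagement will look harmful even when it helps. The sign of a real benefit flips only under strong confounding: a true 0.6 exceeds 1 in just one cell of the step 4 table. The other is that the trial's main result is at risk. The primary comparison rests on randomized crossover order and does not use path b. The affected analyses are mechanistic, but they test the article's stated explanation of how the intervention works, so the change is worth making before the data are analyzed.

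**What to change.** In the mediator and outcome models of every mediation analysis (engagement, documented interventions, crisis use):

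1. Add baseline risk measured at or before the index visit: the MHRN model score, computed for both exposed and unexposed visits; past-year suicide attempt; current mental health diagnoses; and PHQ9 item 9, with missing values handled by the imputation already planned.
2. Do not rely on follow-up visit frequency as the severity adjustment in path b.
3. State the assumption of no unmeasured mediator–outcome confounding, and report a sensitivity analysis for departures from it.

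The cost is wording plus a little more analysis. History and diagnoses come from records the sites already hold, and the score is computed from the same kind of data. The main practical burden is missing item 9.

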### Implementation outcomes

There is little published guidance on how suicide risk models should be implemented in clinical settings. Work we completed in preparation for this implementation trial gave us insights into what patients and clinicians thought about the possible use of such models in clinical care [35–38]. The Technology Acceptance Model [52] posits that perceived usefulness of a technology positively influences use intention, which then drives adoption [53]. Perceived usefulness is one aspect of appropriateness of an intervention, and together these operate among many interacting components (e.g., burden, ethicality and fit with value system, knowledge) to influence acceptability [54], a necessary but insufficient condition for use and effectiveness. Beliefs about appropriateness and acceptability are influenced by the sociocultural context and perceived norms within which the technology user operates [53, 54]. Of course, feasibility of an intervention also affects use. Use is a precondition for reach and effectiveness, and acceptability, feasibility, and effectiveness may contribute to overall sustainability.

We will measure these outcomes by surveying clinicians who will be exposed to the intervention (e.g., therapists, psychologists, psychiatrists) prospectively (2–4 weeks prior to implementation) and concurrently with use (six months after implementation begins). To reduce clinician burden, we chose a parsimonious set of validated implementation measures (< 40 items). The Perceived Usefulness Scale [55] consists of 6 items with high reliability [Cronbach’s α = 0.98] and high convergent, discriminant, and factorial validity. The Intervention Appropriateness Measure [56] (IAM, 4 items), Acceptability of Intervention Measure [56] (AIM, 4 items), and Feasibility of Intervention Measure [56] (FIM, 4 items) trio have demonstrated content validity, discriminant content validity, reliability, structural validity, structural invariance, known-groups validity, and responsiveness to change. Higher scores indicate greater acceptability, appropriateness, and feasibility. The Intervention Usability Scale [57] (IUS, adapted from the System Usability Scale [58], 10 items) can effectively differentiate between usable and unusable interventions. A score of > 70 will be considered adequate usability. And, pre-implementation only, the Organizational Readiness to Change [59] (ORIC) scale measures an organization’s readiness to implement a change to their current processes; higher scores indicate greater readiness. Adoption will be measured at the clinic level as the proportion of clinics (out of total clinics) that implement the risk model, with 75% as a benchmark. Sustainment will be measured six months after the intervention phase ends by determining the number of clinics continuing to use the risk model, with 75% as a benchmark.

### Analysis plan for implementation outcomes

We will use descriptive statistics (frequencies and crosstabs) to summarize and compare clinician survey results prior to and following six months of intervention use. To compare clinician sentiment about the use of suicide risk models in clinical care we will use General Linear Models for repeated measures using the Greenhouse-Geisser test for within-subjects effects. We will document pre-implementation decision-making and adaptions during the implementation period, should they occur, in a series of reports.

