The study will also collect implementation data as part of the process of evaluating the intervention in three health systems. We will collect information during the start-up period (to document current usual care for suicide prevention and local implementation decisions), during the intervention period (to collect information on adaptations, should they occur), and during the sustainment period (to capture lessons learned and whether and how the intervention endures). Data will be collected in the form of meeting minutes, observations, and field reports from clinical leads and champions. Additionally, surveys of clinicians who will work with the suicide risk model intervention will be conducted prior to implementation and six months following implementation.

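### With only two clinician surveys the Greenhouse-Geisser correction has no effect, and the repeated-measures GLM is a paired t test that uses only clinicians with both surveys

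*Protocol article*

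**What the plan says.** The protocol article, under Implementation outcomes, surveys clinicians "prospectively (2–4 weeks prior to implementation) and concurrently with use (six months after implementation begins"). Objectives and hypotheses gives the same two time points: surveys "will be conducted prior to implementation and six months following implementation". One instrument is given once only ("pre-implementation only, the Organizational Readiness to Change" scale), so it adds no further occasion.

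Under Analysis plan for implementation outcomes, descriptive statistics are to summarise and "compare clinician survey results prior to and following six months of intervention use". Clinician sentiment is then compared with "General Linear Models for repeated measures using the Greenhouse-Geisser test for within-subjects effects". No third occasion and no other within-clinician factor is named.

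The missing-data provision, "We will address missing data using multiple imputation or inverse probability weighting, depending on the nature and extent of missingness", closes the analysis plan for effectiveness outcomes. It is not repeated or referred to in the plan for the surveys. Under Ethical considerations, a clinician consents by submitting a survey, so taking part is a separate choice each time.

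**The concern.** The Greenhouse-Geisser correction protects a repeated-measures F test against unequal variances of the differences between occasions. That problem needs at least three occasions, and here there are two. The one inferential detail given for the surveys therefore does no work.

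The procedure that carries it does have a consequence. A repeated-measures GLM needs a complete row for each clinician. With two voluntary surveys more than six months apart, some clinicians will answer only one, and they add nothing to the test of change. What is at stake is some precision, and protection against dropout related to the baseline score, for the perceived usefulness, appropriateness, acceptability, feasibility and usability scales. These are the clinician-level implementation outcomes of a hybrid trial.

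**Working it through.** The article gives no sample size, response rate or power figure for the surveys, so there is no stated figure to reproduce.

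**1. Number of occasions.** From Implementation outcomes and Objectives and hypotheses, k = 2.

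**2. Epsilon.** ε = tr(D)² / [(k − 1) tr(D²)], where D is the double-centred covariance matrix of the occasions; its lower bound is 1/(k − 1). For k = 2, let v be the variance of the within-clinician difference. Then D = (v/4) × [[1, −1], [−1, 1]], tr(D) = v/2 and tr(D²) = v²/4, so ε = (v²/4)/(1 × v²/4) = 1. The lower bound is also 1. In a numerical check on 5,000 random covariance matrices for each k, ε was 1.000 throughout for k = 2, 0.50 to 1.00 for k = 3, and 0.34 to 0.94 for k = 4.

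**3. Equivalence to the paired t test.** On simulated pairs, F = t² = 0.0102, and the uncorrected F, the Greenhouse-Geisser F and the paired t test all gave p = 0.9198. A clinician with one survey has no difference score and so does not enter.

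**4. Clinicians and precision lost when either survey may be missed.** Assumptions, none from the article: response probability p at each survey, independent between surveys; equal variances; within-clinician correlation ρ of 0.3 to 0.7.

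- Both surveys: p². At least one: 1 − (1 − p)². Share with both: p²/[1 − (1 − p)²].
- Variance of mean change, complete pairs: 2(1 − ρ)/p².
- Variance, all available surveys (covariance taken as known): 2/[p²/(1 − ρ) + p(1 − p)].
- SE ratio: √[1 + (1 − ρ)(1 − p)/p].

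| p | Both | At least one | Share with both | SE ratio, ρ = 0.7 to 0.3 |
|---|---|---|---|---|
| 0.5 | 0.25 | 0.75 | 0.33 | √1.30 to √1.70 = 1.14 to 1.30 |
| 0.6 | 0.36 | 0.84 | 0.43 | √1.20 to √1.47 = 1.10 to 1.21 |
| 0.7 | 0.49 | 0.91 | 0.54 | √1.13 to √1.30 = 1.06 to 1.14 |

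**5. Loss only among baseline responders.** If a fraction a of baseline responders is lost and nobody joins later, the SE ratio is √{2/[(1 + ρ) + (1 − ρ)(1 − a)]}. At a = 0.1, ρ = 0.7: √(2/1.97) = 1.01. At a = 0.5, ρ = 0.3: √(2/1.65) = 1.10.

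**6. Bias when follow-up response depends on the baseline score.** With true change zero, the expected complete-pairs change is −(1 − ρ) × (mean baseline score, in SD units, of those who answer again). In a simulation with ρ = 0.5, about half responding, and higher scorers more likely to respond (logit slope 0.5 or 1.0 per SD), complete pairs showed −0.12 and −0.20 SD. The all-available likelihood estimate was about 0. If lower scorers were more likely to answer again, the sign would reverse.

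**7. Clinic.** A clinic effect that is the same on both occasions cancels from each clinician's difference. With 20 clinics of 8 clinicians (assumed), ρ = 0.5 and unit variance apart from clinic, the SE of mean change from complete pairs is √(2 × 0.5/160) = 0.0791, whether the clinic intercept variance is 0 or 0.3. Only clinic variation in change alters it.

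**The case against.** The strongest reply is that a redundant correction harms nothing: the paired comparison is valid for those who answer twice, and removing the Greenhouse-Geisser wording alone changes no estimate, interval or p value. That stands.

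It can also be said that a condensed article need not spell out how partial responders are handled. That is fair for detail left unsaid, but here a method is named, and complete pairs are what that method uses. A reader might infer that the plan states single-survey clinicians will be discarded. It does not: they would still appear in the descriptive tables, and imputation or weighting could be extended to the surveys, though its placement does not say so.

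A reader might also infer that clinicians who dislike the tool will leave, so the results will flatter it. Nothing in the article documents such a pattern. If response did rise with baseline favourability, complete pairs would show a false decline.

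Nor do the working figures support reading the 33–54% share as the information retained, because single-survey clinicians carry little information about change when correlation is high. The independence assumption is also pessimistic: overlap rises if the same clinicians tend to answer both times.

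On clustering, it is right that a clinic random intercept alone would leave the standard error of change essentially as it is. The article gives reasons to expect differences between clinics: Overview of study design links local training rigor to acceptability and feasibility. It does not show that change varies by clinic, and a repeated-measures GLM could carry site or clinic as a between-subject factor.

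**Conclusion.** The point holds as a minor one. It is certain that the Greenhouse-Geisser step is inert with two occasions and that the named time test is a paired t test on clinicians with both surveys. The size of the loss cannot be derived from the article. Under the stated assumptions the standard error is about 6% to 30% larger than with all available surveys, and only 1% to 10% larger if the sole loss is follow-up dropout among baseline responders. A false change is possible if response depends on the baseline score, but neither its occurrence nor its direction can be read from the article. Clinic-level adoption and sustainment, the descriptive survey summaries and the suicide-attempt analyses do not depend on this test.

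**What to change.** For each scale measured twice, fit a linear mixed model to all available surveys, with time (before, six months) and site as fixed effects and a random intercept for clinician. Allow for clinic clustering of change with a clinic-by-time random effect or clinic-robust standard errors. Drop the Greenhouse-Geisser step.

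The cost is a change of wording and standard software, with no further data collection. One limit should be stated: the model assumes that missing surveys are missing at random, so it does not remove bias from non-response that depends on the unobserved six-month opinion.
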